## Abstract

**Objectives:**

The general consensus is that surgical treatment is advised when conservative methods fail in patients with lumbosacral radicular syndrome (LRS). Preliminary evidence from our pilot study indicates that combination therapy (mechanical diagnosis therapy and transforaminal epidural injections) can prevent surgical treatment in patients on the waiting list for surgery. The pilot study lacked a control group, and therefore, firm conclusions pertaining to effects could not be made. This study aims to determine if combination therapy, performed while being on the waiting list for lumbar herniated disc surgery, is effective and cost‐effective compared with usual care (i.e., no intervention while being on the waiting list) among patients with a magnetic resonance imaging (MRI)‐confirmed indication for a lumbar herniated disc surgery.

**Methods:**

A randomized controlled trial will be conducted with an economic evaluation. Patients aged 18 and above with incapacitating LRS, with leg pain and an MRI confirmed indication for lumbar disc hernia surgery, will be recruited from seven Dutch hospitals. While being on the waiting list for lumbar herniated disc surgery, patients will be randomized to either the combination therapy or usual care group. The primary outcome measure is the number of patients undergoing lumbar disc surgery during 12‐month follow‐up. Secondary outcomes include back and leg pain intensity (numeric pain rating scale), physical functioning (Roland Morris Disability Questionnaires‐23), self‐perceived recovery (global perceived effect), and health‐related quality of life (EuroQol Five Dimensions Health Questionnaire (EQ‐5D‐5L) and 12‐Item Short Form Health Survey (SF‐12)). For the economic evaluation, societal and health care costs will be measured. Measurements moments are baseline, 1, 2, 4, 6, 9, and 12 months. Data will be analysed according to the intention‐to‐treat principle.

**Conclusion:**

No randomized controlled trials have evaluated the effectiveness and cost‐effectiveness of combination therapy compared with usual care in patients with an indication for lumbar herniated disc surgery, which emphasizes the importance of this study.

## INTRODUCTION

1

Lumbar disc herniation is the most common cause of lumbosacral radicular syndrome (LRS), also known as sciatica. Characteristics of LRS include radiating lower limb pain into a particular dermatome, which may be accompanied by sensory and or motor deficits (Oosterhuis et al., 2014). Evidence suggests that the pathophysiology of LRS is not attributed to just pressure on the nerve roots but to a complex interplay of inflammatory, immunological, and pressure related processes (Stafford, Peng, & Hill, 2007). Estimated LRS incidence rate in Western countries is 5 per 1,000 (Cherkin, Deyo, Loeser, Bush, & Waddell, 1994). In the Netherlands, the incidence rate of LRS in general practice is 12 per 1,000 patients per year (Schaafstra et al., 2015). The yearly direct and indirect costs of LRS are high and estimated to be €1.2 billion in the Netherlands (Health Council of the Netherlands, 1999).

There is a lot of variation in LRS prevalence in literature (Konstantinou & Dunn, 2008). Consequently, there are disparities in spinal surgery rates regionally and internationally (Weinstein, Lurie, Olson, Bronner, & Fisher, 2006). In the United States, spinal surgery rates are 30% higher than in the Netherlands, 80% higher than in United Kingdom, and 50–60% higher than in Canada (Cherkin et al., 1994).

The Dutch guideline “Lumbosacral Radicular Syndrome” recommends surgical treatment if the radiating leg pain persists following conservative management (Kwaliteitsinstituut voor de Gezondheidszorg CBO, 2008). A significant number of patients undergoing surgery for lumbar disc herniation suffer residual complaints. Recovery rates in the literature vary wildly. Recent figures from the Netherlands suggest a rate between 69% and 79% after 2‐year follow‐up, and 10%–15% of the patients need repeated surgery, the majority of which were due to recurrent disc herniation at the same level (Arts et al., 2011). Findings of Peul et al. (2007) indicate that surgical and nonsurgical management of lumbar hernia are equally successful in the long term.

Both mechanical diagnosis and treatment (MDT) and transforaminal epidural steroid injections (TESIs) are reported to be individually effective in reducing pain and improving function among LRS patients (Chou et al., 2015; van Helvoirt et al., 2014). Epidural corticosteroid injections for radiculopathy are associated with immediate reduction in pain (Chou et al., 2015). TESIs are indicated in LRS, and the role of physiotherapy, possibly in combination with TESIs, should be further explored (Kwaliteitsinstituut voor de Gezondheidszorg CBO, 2008). None of the randomized controlled trials included by Chou et al. (2015) combined TESIs with MDT. The only two publications that we identified assessing a combination therapy of TESIs and MDT were our own pilot study (van Helvoirt et al., 2014), and a report on three cases of acute cervical radiculopathy (Desai, Padmanabhan, Simbasivan, Kamanga‐Sollo, & Dharmappa, 2012). Our pilot study suggests that combining these interventions has the potential to reduce the number of lumbar herniated disc surgeries, as only 22% of patients with a herniated lumbar disc still needed surgery after 1‐year follow‐up (van Helvoirt et al., 2014).

Research indicates that the effects of lumbar disc surgery are comparable with those of conservative treatment after 1 and 2 years (Peul et al., 2007; Peul et al., 2008). Clinical guidelines prescribe shared decision making and that pros and cons of both options should be discussed with patients (Kwaliteitsinstituut voor de Gezondheidszorg CBO, 2008; National Institute for Health and Clinical Excellence, 2016). Surgery is costly and potentially causes various side effects (e.g., nerve root damage, infection, and pain that continues after surgery); hence, spinal surgeons typically aim to prolong conservative therapy. Physiotherapists could play an important role in preventing surgery if they combine their treatment with optimal pain management (Schaafstra et al., 2015). Although the results from our pilot study seem to be promising, the effectiveness and cost‐effectiveness of a combination therapy of TESIs and MDT have not been rigorously evaluated. Therefore, this study aims to determine if a combination therapy, while being on the waiting list for a lumbar herniated disc surgery, is effective and cost‐effective compared with usual care (i.e., no intervention while being on the waiting list) among patients with a magnetic resonance imaging‐confirmed indication for a lumbar herniated disc surgery.

## METHODS

2

### Study design

2.1

A multicentre randomized controlled trial with a 12‐month follow‐up and a full economic evaluation.

#### Ethical approval

2.1.1

In September 2017, the Medical Ethics Committee of the VU University Medical Centre Amsterdam approved the study protocol, registration Number NL60558.029.17 and the study was registered in the Dutch Trial Register NTR6715.

### Subjects

2.2

#### Inclusion criteria

2.2.1

Inclusion criteria are as follows: patients aged 18 and above; eligibility for lumbar disc hernia surgery; incapacitating LRS with leg pain (numeric pain rating scale [NPRS] > 6; with or without back pain) that had lasted for a minimum of 6 weeks with or without mild neurological deficit (i.e., Medical Research Council > 3); and a magnetic resonance imaging that confirms a hernia nuclei pulposi that compromises the spinal nerve and can explain the clinical symptoms of the patient.

#### Exclusion criteria

2.2.2

Exclusion criteria are as follows: spine surgery and or transforaminal injections at the same level during the previous 6 months; bony stenosis; cauda equina syndrome; spondylolisthesis; pregnancy; complicated disc herniation requiring more than one operation; severe coexisting disease (e.g., osteoporosis and dementia); patient with contraindications for steroid injections; insufficient knowledge of the Dutch language; emergency surgery as determined by the neurosurgeon; and being allergic for Iohexol 240 mg/ml (i.e., OMNIPAQUE 240).

#### Patient recruitment

2.2.3

Figure 1 shows the flow diagram of the study. Neurosurgeons or orthopaedic surgeons of the participating hospitals recruit and inform the patients about the study and the possibility to participate while they are on the waiting list for surgery. The surgeon then refers the patient to the research team who will check if the patient meets the aforementioned inclusion and exclusion criteria. If the patient is eligible and gives informed consent, the patient will be included in this study. Baseline measures will then be made and patients will be randomized to either the intervention or the control arm of the study.

**Figure 1 pri1796-fig-0001:**
[figure not shown]
Flow chart of the Preventing lumbar disc surgery (PLUS) study

#### Setting

2.2.4

Participants will be recruited from seven hospitals in the Netherlands. The hospitals were chosen due to their proximity to the four primary care‐based outpatient clinics (so‐called “Rugpoli's”) where the combination therapy will be provided.

### Materials

2.3

#### Prognostic factors

2.3.1

Prognostic factors measured at baseline using an online questionnaire include duration and severity of complaints before operation, various psychosocial variables (somatization, distress, and anxiety), and known confounding factors such as age, gender, educational level, and treatment expectation (Kwaliteitsinstituut voor de Gezondheidszorg CBO, 2008).

#### Primary outcomes measure

2.3.2

The primary outcome measure is the proportion of LRS patients undergoing lumbar disc surgery during 12‐month follow‐up. Patients will be scored as either having had a lumbar surgery or not. For this purpose, patients will be asked whether they had a lumbar surgery during the previous weeks following the last assessment, using an online questionnaire at 2, 4, 6, 9, and 12 months after randomization, and validated using hospital records.

#### Secondary outcomes measures

2.3.3

In line with the core outcome set for clinical research and clinical practice (Chiarotto et al., 2018), secondary study parameters include back and leg pain, physical functioning, and health‐related quality of life. Additionally, we will measure self‐perceived recovery, patient satisfaction (single question), and pain location (pain mannequin). Measurements will take place at baseline, 2, 4, 6, 9, and 12 months after randomization and administered through online questionnaires. An additional pain intensity measurement will be carried out at 4 weeks after randomization. The rationale is that, especially leg pain, will improve in the combination group. Complications will be noted in a case report form. Societal and health care costs will be estimated for economic evaluation using resource use data, collected through online questionnaires at baseline, 2, 4, 6, 9, and 12 months after randomization.

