##### Health‐related quality of life (EQ‐5D‐5L and SF‐12)

The EQ‐5D‐5L is a quality of life scale that is responsive for chronic low back pain patients (Soer, Reneman, Speijer, Coppes, & Vroomen, 2012). The EQ‐5D‐5L has five health dimensions: mobility, self‐care, daily activities, pain/discomfort, and anxiety/depression. Within each dimension, the patients can self‐rate their level of severity; no, slight, moderate, severe problems, unable to perform, or do the task (Versteegh et al., 2016). For the economic evaluation, the patients' EQ‐5D‐5L health states will be converted into utility scores ranging from 0 (“death”) to 1 (“optimal health”) using the Dutch tariff (Versteegh et al., 2016).

The SF‐12 is a shorter version of the SF‐36 health‐related quality‐of‐life questionnaire. The SF‐12 has been proven to be a reliable and valid questionnaire for low back pain (Xuemei et al., 2003). The questionnaire relates to the analysis of the general functional status of patients. It consists of 12 questions from the following eight domains: (a) physical functioning, (b) physical role limitations, (c) emotional role imitations, (d) social functioning, (e) physical pain, (f) general mental health, (g) vitality, and (h) general health perception. These eight domains can be summarized into a physical and psychological main domain (Xuemei et al., 2003). For the economic evaluation, quality‐adjusted life years will be calculated by multiplying the patients' time spent in a certain health state by the respective utility value (i.e., area under the curve method).

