##### Societal and health care costs

Societal costs include costs of the intervention, other health care use, informal care, unpaid productivity losses, and costs due to absenteeism (i.e., sickness absence) and presenteeism (i.e., being less productive while being at work). Health care costs will only include costs accruing to the formal Dutch health care sector.

Intervention costs will be microcosted. For this purpose, information about the combination therapy will be gathered using a case report form, including information on patient classification, number of sessions, discharge, and referral to a network MDT or to the surgeon. All other cost categories will be measured using cost questionnaires administered at baseline 2, 4, 6, 9, and 12 months after randomization. Resource use will be valued in accordance with the Dutch manual of costing (Hakkaart‐van Roijen, Tan, & Bouwmans, 2010). See Table 1: overview of the data collection.

**Table 1 pri1796-tbl-0001:** Overview of the data collection

Outcome measures	Baseline	4 weeks	2 months	4 months	6 months	9 months	12 months
Prognostic factors							
Patient demographics and prognostic factors	X						
Primary outcome							
Surgery rate			X	X	X	X	X
Secondary outcomes							
Pain leg (NPRS)	X	X	X	X	X	X	X
Pain back (NPRS)	X	X	X	X	X	X	X
Health‐related quality of life (EQ‐5D‐5L and SF‐12)	X		X	X	X	X	X
RMDQ‐23	X		X	X	X	X	X
Self‐perceived recovery (GPE)			X	X	X	X	X
Societal and health care costs (cost questionnaires)	X		X	X	X	X	X
Patient satisfaction, complications, and pain location	X		X	X	X	X	X

Abbreviation: NPRS, numeric pain rating scale; RMDQ, Roland Morris Disability Questionnaires.

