#### Economic evaluation

2.4.10

An economic evaluation will be performed from a societal and a health care perspective. When the societal perspective is applied, all costs and consequences relevant to the intervention will be taken into account irrespective of whom pays or benefits, whereas only those accruing to the formal Dutch health care sector will be considered when the health care perspective is applied (Hakkaart‐van Roijen, van der Linden, Bouwmans, Kanters, & Tan, 2015; Brouwer, van Exel, Baltussen, & Rutten, 2006).

The economic evaluation will be performed in accordance with the intention‐to‐treat principle and in terms of quality‐adjusted life years as well as the primary outcome proportion of LRS patients undergoing lumbar disc surgery during 12‐month follow‐up. Missing data will be imputed using multiple imputations by chained equations. The imputation model will be constructed in accordance with the recommendations of White, Royston, and Wood (2011). Imputed datasets will be analysed as specified below, after which pooled estimates will be estimated using Rubin's rules (White et al., 2011). Incremental cost‐effectiveness ratios will be calculated by dividing the difference in costs by that in effects. In order to account for the possible clustering of data, analyses will be performed using linear mixed models (Gomes et al., 2012). Accounting for the possible clustering of data (e.g., at the hospital level) is very important, as most economic evaluations fail to do so, whereas ignoring the possible clustering of data might lead to inaccurate levels of uncertainty and inaccurate point estimates (Gomes et al., 2012). Bootstrapping techniques will be used to estimate the uncertainty surrounding the cost‐effectiveness estimates. Uncertainty will be shown by plotting cost‐effect pairs on cost‐effectiveness planes and by constructing cost‐effectiveness acceptability curves (Black, 1990; Drummond, Sculpher, Torrance, O'Brien, & Stoddart, 2005; Fenwick, O'Brien, & Briggs, 2004). Cost‐effectiveness acceptability curves indicate the probability of an intervention being cost‐effective compared with a control for a range of ceiling ratios (i.e., the maximum amount of money decision makers are willing to pay per unit of effect gained).

Various one‐way sensitivity analyses will be performed to test the robustness of the study results (e.g., complete‐case analysis and per‐protocol analysis).

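### EQ-5D-5L is not asked at the 4-week contact, so the QALY calculation has no utility between baseline and 2 months; the resulting error is small, of uncertain direction, and cheap to remove

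*Protocol article*

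**What the plan says.** Section 2.3.3 of the protocol article sets the general questionnaire schedule: "Measurements will take place at baseline, 2, 4, 6, 9, and 12 months after randomization and administered through online questionnaires". It then adds one earlier contact, for pain alone: "An additional pain intensity measurement will be carried out at 4 weeks after randomization". The reason follows: "The rationale is that, especially leg pain, will improve in the combination group".

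Table 1 agrees with this text. The leg and back pain rows are marked at 4 weeks. The row that begins "Health‐related quality of life (EQ‐5D‐5L and SF‐12" is marked at baseline and at 2, 4, 6, 9 and 12 months, and is blank at 4 weeks. The abstract lists 1 month among the measurement times without separating the outcomes; section 2.3.3 and Table 1 show that this point covers pain only.

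The quality-of-life subsection converts EQ-5D-5L states to Dutch-tariff utilities. It forms QALYs by multiplying "time spent in a certain health state by the respective utility value" and calls this the area under the curve method. Section 2.4.10 runs the economic evaluation "in terms of quality‐adjusted life years as well as the primary outcome proportion" of patients operated on, so QALYs are one of two effect measures.

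**The concern.** The protocol added a pain measurement ahead of 2 months, yet 2 months is its first post-baseline point for utility. Several of its own statements put change inside that gap:

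- Section 2.4.1 has intervention patients attend within a week of randomisation.
- The Introduction says of the injections: "Epidural corticosteroid injections for radiculopathy are associated with immediate reduction in pain".
- The TESI procedure brings the patient back two weeks after an injection.
- Controls meanwhile wait for surgery (section 2.4.3), and 93% are assumed to be operated on during follow-up (section 2.4.6). Their utility may therefore shift at a date that this schedule cannot locate.

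EQ-5D-5L has a pain/discomfort dimension, so the change that motivated the 4-week contact is one that utility should also register. If the utility difference between arms does not move in a straight line over the first 2 months, the QALY difference is wrong by the area between the true course and the line. A later analysis plan cannot recover a utility that was never collected.

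**Working it through.** The article states no expected QALY or utility difference, so there is no figure to reproduce. The check asks how far the QALY difference over the first 2 months depends on having a 4-week point.

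**Inputs from the article.** EQ-5D-5L at baseline and 2 months, none at 4 weeks (section 2.3.3, Table 1); QALY by area under the curve (quality-of-life subsection).

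**Assumptions.** Straight lines between measured points; no difference between arms at baseline; a utility difference (combination minus usual care) of d1 at 4 weeks and d2 at 2 months, over a range. Times in years are 4/52 = 0.0769 and 2/12 = 0.1667.

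**Formulas.**
- Area without the 4-week point: 0.5 × 0.1667 × d2.
- Area with it: 0.5 × 0.0769 × d1 + 0.5 × (d1 + d2) × (0.1667 − 0.0769).
- The straight line has the height (0.0769/0.1667) × d2 = 0.4615 × d2 at 4 weeks. The departure from it is h = d1 − 0.4615 × d2.
- Missed area = 0.5 × 0.1667 × h = 0.083h.

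**One case in full.** Take d1 = d2 = 0.10. Without the point: 0.5 × 0.1667 × 0.10 = 0.0083. With it: 0.0038 + 0.0090 = 0.0128. Then h = 0.10 − 0.0462 = 0.0538, and 0.083h = 0.0045, about 35% of the area in that interval (0.0045/0.0128).

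**Range** (last column from unrounded values):

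| Scenario | d1 (4 weeks) | d2 (2 months) | Area without | Area with | Missed |
|---|---|---|---|---|---|
| Gain persists | 0.05 | 0.05 | 0.0042 | 0.0064 | 0.0022 |
| Gain persists | 0.10 | 0.10 | 0.0083 | 0.0128 | 0.0045 |
| Gain persists | 0.20 | 0.20 | 0.0167 | 0.0256 | 0.0090 |
| Gain half closed | 0.20 | 0.10 | 0.0083 | 0.0212 | 0.0128 |
| Gain closed by 2 months | 0.10 | 0 | 0 | 0.0083 | 0.0083 |
| Gain closed by 2 months | 0.20 | 0 | 0 | 0.0167 | 0.0167 |
| Gain closed by 2 months | 0.30 | 0 | 0 | 0.0250 | 0.0250 |
| Gain only after 4 weeks | 0 | 0.10 | 0.0083 | 0.0045 | −0.0038 |

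With d2 = 0.10 the error is zero at d1 = 0.0462. Above that the straight line understates the gain from the combination therapy; below it, the line overstates the gain.

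**The case against.** The strongest reply is that nothing here is an error. The text and Table 1 agree, there are six EQ-5D-5L points in a year with closer spacing early, and a short pain-only contact is a reasonable way to limit burden. That stands: this is a design choice that could be improved, not a contradiction. The article also does not state linear interpolation; that is the usual reading of the method it names.

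Three stronger readings are tempting, and the documents support none of them.

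- *That the protocol expects its largest difference at 4 weeks.* It says only that pain, leg pain above all, should improve in the combination group. It names no peak and says nothing about utility. The remark on immediate effect concerns pain after injections, and only patients classed as noncentralizers start with injections; centralizers start with directed exercise. The treatment course may even point later. Assume a first injection at week 1, further ones at each two-week review, and then the average 4 weeks of exercise sessions. A one-injection patient finishes at about week 1 + 2 + 4 = 7 and a three-injection patient at about week 1 + 6 + 4 = 11.
- *That the gap biases the QALY against the combination therapy.* This holds only if the early difference lies above the line. If benefit comes after 4 weeks, the sign reverses. A postoperative dip and recovery in controls before 2 months would also go unseen. The largest losses require the gap to close by 2 months, hence most controls operated on and improved by then. The waiting time is not given, and the 93% refers to the whole follow-up. If controls are still waiting at 2 months, the gap persists and most of it is captured.
- *That the cost-effectiveness question rests on QALYs alone.* Section 2.4.10 also uses the proportion operated on, which this gap does not touch.

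The objection therefore limits the size and removes any claim about direction. It does not remove the gap, and uncertainty about the early course is itself a reason to measure it.

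**Conclusion.** The point holds as a modest, correctable weakness. No utility is observed between baseline and 2 months, although treatment begins within a week and the protocol anticipates early pain improvement. The error in the QALY difference is 0.083 times the departure of the 4-week utility difference from the straight line, anywhere from about 0.004 QALY overstated to 0.025 missed across the scenarios tabulated. These figures rest on assumed utilities, no difference at baseline and linear interpolation, and which scenario applies depends partly on a waiting time that the article does not give. The consequence is confined to the QALY results and the early description of quality of life. The primary surgery outcome, the sample size and the cost-effectiveness result per operation avoided are unaffected.

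**What to change.** Add EQ-5D-5L to the 4-week contact in both arms, amend section 2.3.3 and Table 1 to match, and compute the area-under-the-curve QALY from baseline, 4 weeks and 2, 4, 6, 9 and 12 months. State the interpolation between points in the same place.

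For patients already past 4 weeks, the 4-week utility can enter the multiple imputation planned in section 2.4.10, with the 4-week leg and back pain scores as predictors, but only if enough later patients supply observed values. The article does not give recruitment status. If too few remain, keep the existing QALY as the main analysis and report a sensitivity analysis of the first interval, informed by the 4-week pain scores that are collected anyway.

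The cost is five more items at a contact that already takes place (presumably online like the others, though the article does not say so), a minor amendment, slightly more patient burden and one more time point to impute. The sensitivity analysis needs no new data.
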